### Trial inclusion and exclusion criteria

According to the eligibility criteria for the enrolment in the NWpG care programmes patients will be included in the study if they have been diagnosed as having a mental illness of the categories F20-F29, F30-F39, F40-F48, F50, F60-F62, F68-F69 and F91- F94 after ICD-10 during the last 12 months. Patients with a primary diagnosis of substance use disorder (F10-F19, ICD-10) will be only included if they have a psychotic disorder due to substance use.

In addition, patients should have either had a psychiatric inpatient admission or an ambulatory prescription of antipsychotic, anxiolytic or antidepressant drugs during the last 12 months.

Patients must be in the age range of 18 to 80 years, and patients with a care level are excluded.

Group allocation is performed on the basis of the type of care provision intended for the coming 18 months.

### Trial recruitment process

A total of 500 patients, in detail 50 IC patients and 50 CAU patients in each of the five regions and half as many (250) relatives will be recruited via multiple settings. Recruitment will be organised by local research associates. The patients for the intervention group will be informed about the study mainly at introductory sessions for general registration for integrated care by service providers. Patient recruitment for the control group occurs with the assistance of cooperating psychiatric/psychosocial institutions (e.g. resident physicians and socio-psychiatric services). Moreover, patients who decline integrated care after the introductory session will be asked to participate in the control group. Posters and flyers advertising the study are also distributed at potential recruitment sites (e.g. medical practices).

Cooperating psychiatric health institutions that agreed to inform their patients about the study will exchange personal contact details of patients interested in the study with the associate on a regular basis. Written patient information is about the aim of the study, benefits and risks of participation and the study procedure. Subsequently, the associate contacts the patient and checks patient eligibility. If patients meet all of the inclusion and none of the exclusion criteria, they are selected for the study, and an appointment for visit 1 will be set. At visit 1, patients are asked to nominate a relative/informal carer who can be contacted by study staff regarding participation in the study. Patients should provide detailed information material about the study to the person nominated. If the person is interested, he or she is asked to contact the local research associate. If there is no reply, research associates will call the patient once again.

### Trial consent procedure

Patients interested in the study can choose either to contact the research associates themselves or to sign a written consent form that contact data can be submitted from cooperating psychiatric health institutions to the research associate and that the research associate is allowed to call the patient.

At the beginning of visit 1, patients will be informed once more with verbal and written information regarding the study, and patients are asked to give written informed consent if they agree to participate in this study. This will be done by local research associates.

Patients are informed that they can withdraw at any time without having to disclose reasons.

Registration in the integrated care programme occurs completely independent of patients’ decision to participate in the study or not.

Patients are asked to nominate an informal carer/relative who can be interviewed with patient approval. Participation of relatives/informal carers requires the written consent of the patient and of the person of reference him- or herself.

### Data collection/management process

In the context of this study patients will be interviewed four times, every 6 months: baseline (visit 1), 6 months (visit 2), 12 months (visit 3) and 18 months after visit 1 (visit 4). The first assessment (baseline, visit 1) in the intervention group should be within the first month patients are registered in the integrated care programme. Follow-up windows are defined as plus/minus 4 weeks for the intended time-point (6 months, 12 months or 18 months). There will be a subgroup-analysis eliminating data collected outside these windows.

All clinical interviews will be conducted in rooms of outpatient institutions or at patient’s homes by trained research associates. Research associates are graduates in psychology or nursing. Outcomes are measured by self-report and face-to-face interviews.

There is the same time sequence of assessments for relatives/informal carers as there is for patients. There are also four assessments: at baseline, 6 months, 12 months and 18 months after baseline. Between the patients’ and the relatives’ visits, there should be less than four weeks. Outcomes are rarely measured in face-to-face interviews. Mostly, relatives/informal carers fill out the questionnaires on their own and send them by mail - if necessary specific issues are clarified by phone.

### Quality assurance

All research associates were issued with several standard operating procedures as to good clinical practice, recruitment, realisation of study visits, completion of questionnaires and of study documents, etc. A special training (e.g. training in HoNos evaluation) of the research associates is part of several project meetings. The study coordinator oversees the whole study process by communicating frequently with research associates as regards outstanding issues, checking the data collection procedure and sending queries if necessary. Some on-site monitoring visits are planned. During the whole study process research associates are tested for inter-rater reliability for HoNos using case vignettes.

### Planned analysis

A detailed statistical plan will be developed and put down in writing prior to the analysis of data. Data capturing is performed using IBM SPSS 21. Data analysis will be carried out using IBM SPSS 21, STATA 12 and SAS 9.3.

Baseline characteristics of the study population will be summarised separately within each study group. Categorical baseline variables will be compared between intervention and control group using chi-square tests. The continuous variables will be compared using t-test and Mann–Whitney U test. Descriptive statistics of all outcomes will be provided for all study groups at different time points. Outcomes will be summarised in terms of the total scores, and the proportion of patients improving from baseline.

The main analysis will be conducted on the intention-to-treat (ITT) population.

#### *Measures for bias control*

Adjustment based on the propensity score method will be used to control the selection bias [29]. The estimation of propensity scores will be made on the basis of logistic regression models including independent variables such as medical history, patient’s clinical condition, socio-demographic characteristics and current living conditions [28].

#### *Dealing with missing values*

Missing values will be handled using the method of multiple imputations [30]. Missing data will be imputed 10 times. Then, each of the completed datasets will be analysed using the proposed statistical method. Final results will be drawn from the average analysis of each of the completed datasets using Rubin’s Rule.

#### *Statistical analysis*

The primary outcome is the change in empowerment total score of EPAS over 18 months. Normal distribution is assumed. This will be checked, and if found to be lacking than appropriate solution strategies will be applied. Data analysis for the primary outcome will be performed using analysis of variance with repeated measurements with a time effect, a group effect and an interaction effect between time and study group.

In addition, secondary analysis for the primary outcome will include a per-protocol (PP) approach. The PP population will exclude all subjects in the ITT population who meet any of the following criteria:

– change of study group during study process

– non-compliance or infrequent use of integrated care by volunteers in the IC group

– more than four weeks between registration to integrated care and visit 1 for patients in the IC group

– visit 2, visit 3 and visit 4 were outside initially planned time periods (more than +/− 1 month to intended time points: 6 months, 12 months or 18 months after visit 1)

This additional analysis assesses the maximal intervention efficacy in ideal conditions based on comparable outcome measurements.

For secondary endpoints mixed-effect regression models will be used. The random effect of time as well as the interaction effect of time and study group will be adjusted for propensity scores [28].

Within the frame of health economic evaluation based on the net benefit approach, multivariate regression models for the cost-utility relation as dependent variable will be calculated adjusted for the propensity scores. The cost-utility relation is defined as the ratio of direct and indirect costs and the change in QALYs [31-34]. Change in QALYs will be calculated on the basis of EQ-5D questionnaire. All costs will be calculated from a societal point of view, for that reason total costs of care were considered and not just out-of-pocket payments. Furthermore, production losses due to time off work for those in employment will be included in the analyses.

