**Methods:**

In this 18-month multi-centre observational trial 250 patients enrolled in an integrated mental health care programme and 250 patients who receive treatment as usual from five catchment areas will be included. In addition, in each group about 125 relatives of the participating patients will be included. The primary outcome criterion is the improvement of empowerment; secondary outcomes are subjective quality of life, functional impairment and costs of illness. Data will be collected at baseline and three follow-ups after 6, 12 and 18 months. Data will be analysed by means of mixed effects regression models. Propensity score methods are used for selection bias control.

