### Sample Size calculation

The sample size calculation is performed for the change in the empowerment total score over 18 months. An effect size of f = 0.2 was assumed to be clinically relevant for the within-between interaction of group*time in repeated-measurements ANOVA with two groups and four time-points of measurement.

Based on this effect size, a power of 0.90, and an alpha level of 0.05, a total sample size of n = 350 is needed. Sample size was further estimated based on a drop-out rate of 30 %, according to experience from the ELAN-study [27,28]. Based on this assumption, a total of 500 patients will be recruited for visit 1. The sample size was calculated using G-Power.

All participating patients will be asked to nominate a relative/informal carer who has regular contact with the patient and who supports the patient with regard to disease-related burden. It is expected that relatives/informal carers of about 50 % of patients will participate in the study. Thus, the sample size for persons of reference will be equal to n = 250. Using a repeated-measurements design with four time-points of measurements this sample size will concede the demonstration of an effect with effect-size f = 0.2 and a significance level of alpha = 0.05 with a power greater than 0.75.

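### The primary outcome is change in EPAS over 18 months, but the powered and planned test is an omnibus 3-df group-by-time interaction that does not specifically test it

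*Protocol article*

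**What the plan says.** The Abstract (Methods) gives the aim a direction: "The primary outcome criterion is the improvement of empowerment". The Statistical analysis section gives the measured form: "The primary outcome is the change in empowerment total score of EPAS over 18 months". It then names the model as "analysis of variance with repeated measurements with a time effect, a group effect and an interaction effect between time and study group". It lists the three effects without saying which one decides.

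The Sample Size calculation section supplies that link. It powers the "within-between interaction of group*time in repeated-measurements ANOVA with two groups and four time-points of measurement", with "An effect size of f = 0.2 was assumed to be clinically relevant" and "a power of 0.90, and an alpha level of 0.05, a total sample size of n = 350 is needed".

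No section names a visit, a contrast or an effect estimate on which the primary conclusion will rest. The Planned analysis section says that a detailed statistical plan will be written before the data are analysed.

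**The concern.** With two groups and four visits, the interaction asks whether the two mean profiles are non-parallel in any way. A reader of the trial wants to know whether patients in integrated care gained more empowerment over the 18 months. A yes to the first question does not imply a yes to the second, because the F statistic responds to the size of the departure from parallel profiles and not to its shape. A difference that appears in mid-trial and is gone by month 18 counts as much as a lasting gain of the same noncentrality.

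At stake is how a significant primary result can be read. Without a named contrast, the step from a significant interaction to a claim of improvement would rest on inspecting the means afterwards.

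**Working it through.** **Inputs from the article.** f = 0.2, power 0.90, alpha 0.05, N = 350, 30% drop-out, two groups, four visits (Sample Size calculation); equal groups (Trial recruitment process), so 175 evaluable per group.

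**Assumptions, because the article gives no figure.** EPAS SD 1; equal correlation rho between visits, 0.5 with a range to 0.7; complete data; no propensity adjustment.

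**1. The plan's own figure.**
- Interaction df = (2 − 1)(4 − 1) = 3; error df = 3 × (350 − 2) = 1044.
- Noncentrality: lambda = f² × N = 0.04 × 350 = 14.
- The noncentral F gives power 0.895 at N = 350, and N = 356 for 0.90. This agrees with the article within rounding.
- 350/(1 − 0.30) = 500, the recruitment target.
- For 250 relatives, lambda = 0.04 × 250 = 10 and power is 0.759, which matches the article's statement of more than 0.75.
- A 1-df comparison at f = 0.2 would need 265, and the group main effect 127 to 206 for rho 0.3 to 0.7. The stated N therefore fits the 3-df interaction and neither of these.

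**2. A difference that vanishes by month 18.** For group differences d_t (integrated care minus usual care) and n per group,

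lambda = (n/2) × Σ(d_t − mean d)² / (1 − rho).

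- Profile 0, d, d, 0 at months 0, 6, 12, 18: the mean is d/2 and the sum of squares is 4 × (d/2)² = d².
- Setting lambda = 14: d² = 14 × 0.5/87.5 = 0.08, so d = 0.283 SD.
- At rho 0.7: d² = 14 × 0.3/87.5 = 0.048, so d = 0.219 SD.
- Power of the 3-df test is 0.895 in either case. The true difference in 18-month change is zero, so a 1-df test of it rejects at 5%.
- The mirror profile 0, −d, −d, 0 has the same lambda and so the same power.
- Simulation of 4,000 trials (rho 0.5): the interaction rejects in 89.7%, and in 89.2% for the mirror profile; the test of 18-month change rejects in 5.0% and 4.8%.

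**3. Power of an 18-month contrast when the effect is of the planned size.** The standard error of the difference in change is sqrt(4(1 − rho)/n) = sqrt(4 × 0.5/175) = 0.107.

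- *Steady gain* 0, d/3, 2d/3, d: the sum of squares is (5/9)d². With lambda = 14, d² = 0.08/(5/9) = 0.144 and d = 0.379. The ratio 0.379/0.107 is 3.55, so power is 0.943, against 0.895 for the interaction.
- *Early sustained gain* 0, d, d, d: the sum of squares is 0.75d². Then d² = 0.08/0.75 = 0.107 and d = 0.327. The ratio is 3.06, so power is 0.861, against 0.895.

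With lambda held at 14, the powers in step 3 are the same at rho 0.7. Only the SD differences that they correspond to change.

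**The case against.** The strongest reply is that outcome and test agree if change over 18 months means the whole course over the four visits. The Sample Size calculation section moves directly from the one to the other, and no section defines the outcome as month 18 minus baseline. This reply stands in part. A reader might infer that the planned test does not test the outcome at all, and the article does not support that: the interaction does test differential change, and the 18-month contrast is one of its components. The exact statement is that it does not specifically test it.

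Two other strong readings also fail. One might object that an F test has no direction, but a two-sided 1-df test also rejects for harm, and the article promises descriptive results by visit and the proportion of patients improving from baseline. One might also infer an inflated type I error from non-sphericity, but the article never says that the ANOVA will be uncorrected, and such a correction is ordinary analysis-plan detail.

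The defence can add that the 3-df test is neutral as to shape, and that the article does not say which time course it expects. That is fair. It is why the proposed contrast loses some power for an early sustained gain.

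Leaving the matter to the later analysis plan answers only part of the point. Intervals and follow-up contrasts belong there. But the article itself fixes the outcome, the model and the powered term, and a plan that made an 18-month contrast primary would be changing the primary test. It should say so.

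**Conclusion.** The point holds as a mismatch of emphasis between outcome and test, not as an error in a figure. The sample size is reproduced. The planned interaction reaches its full design power of 89.5% for a mid-trial difference of about 0.28 SD (rho 0.5) or 0.22 SD (rho 0.7) that is gone at month 18, so its significance alone would not support a claim of improvement over 18 months. The SD sizes rest on an assumed SD of 1 and equal correlations. That the power is the same for lasting and vanishing profiles of equal noncentrality does not depend on the value of rho. This is an inexpensive improvement worth making, not a flaw that invalidates the design.

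**What to change.** Before data are analysed, name one primary 1-df comparison: the propensity-score-adjusted difference between groups in EPAS change from baseline to 18 months, with its 95% CI, from a mixed model with unstructured covariance that uses all visits. Keep the 3-df interaction as a supportive description of the time course, and record the change of primary test openly.

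The cost is wording. The article already plans mixed-effects regression for the secondary endpoints and propensity adjustment against selection bias, so no new method is needed. For a steady gain the 500 patients suffice, with about 0.94 power. The downside is lower sensitivity to purely transient effects and, for an early sustained gain, power of about 0.86 on the unadjusted change score, a little under the 0.90 target.

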## Methods/design

### Study design

Although the randomised clinical trial is considered the gold standard for examining the efficacy of mental health care interventions, legal and organisational aspects prevent this design being applied in the current study: The implementation of integrated care programmes took place on the legal basis of the German social code which authorises the health insurances to define the criteria for the eligibility of patients to enrol in integrated care programmes. In addition, the social code gives patients the right to be informed by sickness funds about the opportunity to enrol in an integrated care programme. If a patient fulfils the eligibility criteria, he or she will be informed by the health insurance and asked for the permission to transmit his or her contact data to the local integrated care provider. After the patient gives his or her permission to the sickness fund the local service provider contacts the patient and invites him or her to attend an informative meeting. On the basis of this interview the service provider decides if the patient will be offered enrolment or not. Finally, the patient decides whether to enrol or not.

Therefore, we decided to design this study as a prospective observational controlled trial comparing patients with severe mental disorders enrolled in an NWpG integrated care programme with patients who received standard care in five federal states (Schleswig-Holstein, Northrhine-Westfalia, Berlin, Saxony and Bavaria) covering a broad range of catchment areas with different levels of urbanization, with different local mental health service systems and with different providers of ACT services. Trial duration is 18 months. Data will be collected at baseline and there will be three follow-ups after 6, 12 and 18 months.

Due to preference-based allocation blinding of patients is not feasible. Furthermore, it is not possible to blind the research associates because they would be unblinded at the latest documenting integrated care service use in the Client Socio-Demographic and Service Receipt Inventory (CSSRI).

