## Discussion

This multi-centre controlled study examines the effectiveness and efficiency of contracts of integrated care in patients suffering serious mental illnesses in routine care surroundings. This is the first independent trial in Germany examining the impact of integrated care programmes pursuant to NWpG contracts on empowerment, quality of life, patient satisfaction and health economic measures.

As a major strength of this study, the effectiveness and the efficiency of integrated mental health care will be observed under real world conditions. Research in real life conditions might be more difficult but it will pay off further effort when it comes to external validity of the results. Since the intervention will be delivered by the local integrated care providers in the regional community mental health setting, it can be expected that service provision varies in spite of the fact that the same basic service components have to be provided in each region. In addition, study regions vary with regard to available standard care services and general living circumstances. Furthermore, the study sample will reflect the full heterogeneity of patients with severe mental illness. This heterogeneity of the real world setting provides the opportunity to examine the impact of a broad range of individual and environmental characteristics on the outcome of mental health care.

To make full use of this potential, high levels of academic rigour will be maintained by the involvement of independent, trained research associates and the application of standardised measurement tools, a strict monitoring and quality control for data collection and management and the application of advanced statistical methods for data analysis.

The preference-based allocation of study participants might be the major target of criticism as it is suspected to introduce a selection bias. Preference-based allocation was mainly chosen due to the legal and organisational framework of NWpG contracts in Germany. But it also holds the benefit of reality proximity of the intervention and thus contributes to external validity of study results. Selection bias will be controlled by means of propensity score adjustment. However, it cannot be guaranteed that all factors possibly causing a selection bias can be measured and included in the analysis.

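### The primary repeated-measures ANOVA is specified without the propensity score that the article promises study-wide, leaving the group x time test open to confounding of change

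*Protocol article*

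**What the plan says.** Study design explains why patients are not randomised: insurer, provider and patient all take part in the decision to enrol. It describes the allocation as preference-based ("Due to preference-based allocation blinding of patients is not feasible").

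On control of the resulting bias, three places speak for the whole study:

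- Abstract, Methods: "Propensity score methods are used for selection bias control".
- Measures for bias control: "Adjustment based on the propensity score method will be used to control the selection bias".
- Discussion: "Selection bias will be controlled by means of propensity score adjustment".

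Statistical analysis then defines the endpoint ("The primary outcome is the change in empowerment total score of EPAS over 18 months") and its model: "analysis of variance with repeated measurements with a time effect, a group effect and an interaction effect between time and study group". For the secondary endpoints it switches to mixed-effect regression and adds: "The random effect of time as well as the interaction effect of time and study group will be adjusted for propensity scores". The health economic regressions are also said to be adjusted for propensity scores. The Abstract makes no such distinction between endpoints: "Data will be analysed by means of mixed effects regression models".

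Sample Size calculation uses the group x time interaction of a repeated-measures ANOVA with two groups and four time points, and mentions no covariate.

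**The concern.** The primary model is fixed by listing its terms, and the propensity score is not one of them. It is written in for the other two groups of analyses in the same section. A programmer working from that section would adjust the secondary and economic results but not the primary one. That would not honour the three general statements.

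In a self-selected comparison this matters. Integrated care patients should be assessed within a month of registering for a new programme. Controls come from cooperating institutions, from posters and flyers, and from patients who declined the programme; no comparable starting event is described for them. Different courses of empowerment are therefore plausible without any treatment effect. Such a difference would enter the group x time test directly, biasing the estimate and raising its false-positive rate.

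**Working it through.** **1. Which model was the trial sized on?** Inputs from Sample Size calculation: f = 0.2, alpha 0.05, power 0.90, 2 groups, 4 time points, stated n = 350, drop-out 30%.

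- Noncentral F test with df1 = (2 - 1)(4 - 1) = 3, df2 = 3(N - 2) and lambda = f² x N, assuming sphericity.
- At N = 350, lambda = 0.04 x 350 = 14.0 and power is 0.895. Power reaches 0.90 at N = 356.
- Drop-out: 350 / 0.70 = 500.

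The stated figures reproduce to within 2%. They match the three-term ANOVA with no covariate, so there is no sample-size error here.

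**2. What does group x time remove?** Suppose patient i has a confounder X_i with a level effect a and a change effect s:

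Y_it = a·X_i + s·X_i·t + patient effect + error, with t running from 0 (baseline) to 1 (18 months).

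The change from baseline to 18 months is s·X_i plus error; a cancels. With a group imbalance of d in X and no treatment effect, the expected group difference in change is d x s. If s = 0 there is no bias.

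**3. How large could it be?** The documents give neither d nor s, so these are assumptions: d = 0.3 to 0.5 SD, and s = 0.2 to 0.4 outcome units per SD of X. Given X, the outcome has variance 1 at each visit, half between and half within patients. Simulation used N = 350, 3,000 runs per setting and no true effect:

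| d | s | Bias d x s | Type I error, three-term model | With X x time added |
|---|---|---|---|---|
| 0.3 or 0.5 | 0 (level only) | 0 | 0.046 to 0.049 | not run |
| 0.3 | 0.2 | 0.06 | 0.068 | 0.049 |
| 0.3 | 0.4 | 0.12 | 0.141 | 0.045 |
| 0.5 | 0.2 | 0.10 | 0.106 | 0.056 |
| 0.5 | 0.4 | 0.20 | 0.330 | 0.049 |

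Analytical check of the last row:

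- For t = 0, 1/3, 2/3, 1 the sum of squares about the mean is 5/9.
- The mean within-patient variance is 0.5 + 0.4² x (5/9)/3 = 0.530.
- lambda = (350/4) x 0.20² x (5/9) / 0.530 = 3.67, which gives a rejection rate of 0.330, as simulated.

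**4. Does the form of adjustment matter?** In a mixed model, a term g·PS_i that is constant over time subtracts out of Y_i,18 - Y_i,0. With balanced data, such as after the planned multiple imputation, a score main effect alone therefore leaves the time x group estimate unchanged. Score x time, or weighting, acts on change.

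**5. What does adjustment cost?** Take effective N = 350(1 - R²), where R² is the share of group membership explained by the covariates. R² is assumed, and no reduction in residual variance is counted:

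| R² | lambda = 0.04 x 350(1 - R²) | Power |
|---|---|---|
| 0.05 | 13.3 | 0.877 |
| 0.10 | 12.6 | 0.858 |
| 0.20 | 11.2 | 0.810 |
| 0.30 | 9.8 | 0.749 |

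**The case against.** The best defence is that Measures for bias control is a general section. It stands next to Dealing with missing values, which plainly applies to the primary outcome although the primary model description does not repeat it. Read that way, the ANOVA is propensity-adjusted and only the form is unstated. That form could be left to the detailed statistical plan announced under Planned analysis. This stands in part. A reader might infer that the sponsor chose an unadjusted primary analysis, and no sentence says so. But the section does more than omit a detail: it lists the primary terms, repeats the adjustment for the other analyses, and departs from the model class named in the Abstract.

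A second objection is that group x time already deals with selection. It does for stable level differences, as the first row of the simulation table shows. A reader might infer that the primary result must carry the selection bias; that goes too far, since only confounding of change remains and its size is unknown. The error rates follow entirely from the assumed d and s. More extreme assumptions give larger rates, but the documents support no particular value.

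Third, one might infer that entering the score as an ordinary covariate could never help. That holds for a mixed model with a score main effect only. In the usual general-linear-model form of repeated-measures ANCOVA, a between-subject covariate enters each within-subject contrast and so already acts as covariate x time. The wording for the secondary endpoints, which speaks of adjusting the interaction, may mean the same and is not shown to be wrong.

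**Conclusion.** The point holds as an inconsistency with consequences at the primary endpoint. The model as written lacks the adjustment promised in three places, and it conflicts with the mixed-model statement in the Abstract. If followed literally, it leaves the decisive test open to confounding of change in a study whose Discussion itself names selection bias as the likely main criticism.

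Under the stated assumptions the type I error at 350 patients is about 7% to 33%, against about 5% with level-only confounding. These figures illustrate the exposure; they do not predict this trial's bias. The return to about 5% after adjustment assumes that the confounder is fully measured, which the Discussion says cannot be guaranteed. The sample size of 350 analysed and 500 recruited stands for the model as written. The matter should be settled before the data are analysed.

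**What to change.** - In Statistical analysis, state that the primary model is propensity-adjusted so that the adjustment acts on change: either the score and score x time alongside group, time and group x time, or propensity score weights. If a mixed model is used, say explicitly that a score main effect alone is not the adjustment.
- Keep the three-term ANOVA as a supportive, unadjusted analysis.
- Make the Abstract and Statistical analysis name the same model class for the primary outcome.

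The change is one of wording and needs no new data. Its cost is some precision: power at 350 falls from about 0.90 to roughly 0.88 to 0.75 for R² of 0.05 to 0.30, less whatever is regained through lower residual variance. The sponsor should acknowledge that loss, and that unmeasured confounding remains.
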